## Abstract

**Abstract:**

**Introduction:**

There are currently no colorectal cancer (CRC) screening recommendations specifically outlined for people with HIV (PWH). Screening measures used for people without HIV (PWoH) have been previously discussed as sufficient for use among PWH, despite observations of higher CRC prevalence and CRC reportedly appearing at earlier ages among PWH in comparison to PWoH. Machine learning (ML) methods are regarded as robust approaches that may enhance predictive performance, particularly in the context of complex or high-dimensional data. This study aims to develop an ensemble ML model to predict CRC risk in PWH using comprehensive nationwide datasets. The model’s predictive performance will be evaluated and compared with a baseline Cox proportional regression model. The better-performing method will be implemented to develop a CRC risk prediction model with the aim of personalising screening recommendations for PWH.

**Methods and analysis:**

The study population will include all PWH and PWoH born between 1940 and 2008, aged 18 or older and living in Sweden sometime between 1983 and 2024. The study population will be linked to six nationwide demographic and healthcare registers. Follow-up will continue until the first incident of CRC, emigration or death. The outcome of interest is CRC. PWH will be matched to negative controls 1:10. A Cox regression analysis will be completed first, and the results will be used as a baseline comparison to the ensemble ML results. A range of ML methods will be used to develop the ensemble model using stacking.

**Ethics and dissemination:**

This study has ethical approval from the Regional Ethical Committee in Sweden (Dnr: 2024-04185-02, 2024-06783-02, 2023-00191-01, 2022-02897-02, 2022-05624-01, 2018/11-31/2). Given that the study is retrospective and register-based, using only pseudonymised data, there are minimal physical, psychological or privacy risks to included individuals. All results will be presented at the population level with no possibility of identification. The results of this study will be submitted for publication in a peer-reviewed journal.

STRENGTHS AND LIMITATIONS OF THIS STUDYThis study will include comprehensive data coverage with >99% of people with diagnosed HIV in Sweden spanning over 30 years of detailed follow-up through high-quality national registers.There has been strong patient involvement through a diverse reference group, ensuring alignment with community needs.The study will include all people with HIV in Sweden and therefore the results will be nationally generalisable, as well as potentially to external populations with similar demographics and treatment availability, such as other European countries and Canada.While the integration of multiple machine learning techniques within a robust and comprehensive methodological framework may improve prediction performance, it may reduce model interpretability.The retrospective study design restricts the analyses to preselected variables, limiting the inclusion of any potentially important or confounding factors identified during the course of the study, which could increase the risk of remaining residual confounding.

## Introduction

 Adverse non-AIDS health outcomes are more prevalent among people with HIV (PWH) in comparison to people without HIV (PWoH), including increased incidence of mortality from non-AIDS-related cancers.^1^ Notably, an increased risk of cancers has been observed among individuals who are on antiretroviral therapy (ART) and virally suppressed.^1^ Prior studies have indicated that this increased risk is probably multifactorial, including risk factors such as HIV-related chronic inflammation, immunosuppression and ART toxicity, but also lifestyle factors.^2
3^

Colorectal cancer (CRC) has been suggested to appear at earlier ages among PWH in comparison to PWoH,^4^ and an overall increased prevalence of CRC among PWH in comparison to PWoH has been observed.^5^ Currently, there are no CRC screening recommendations specifically outlined for PWH. The screening recommendations used for PWoH have been considered sufficient for use among PWH,^6^ despite observations of differences in CRC risk and prevalence between PWH and PWoH. The development of CRC risk prediction models for PWH has the potential to offer personalised screening recommendations.

Comprehensive data including income, civil status, migrant status and comorbidities are collected by national Swedish population-based demographic and health registers. The Swedish National HIV register (InfCareHIV) includes detailed biomedical and demographic data collected from more than 99% of people diagnosed with HIV in Sweden.^7^ This register can be linked with other demographic and health data registers in Sweden to accumulate detailed individual-level data for public health analyses.

This study will use comprehensive nationwide data and apply machine learning (ML) methods to develop a CRC risk prediction model. PWoH will be included to increase statistical power. Matching will be used to control for key confounders, and appropriate methods will be applied to minimise bias and prevent overfitting during model development. Sensitivity and subgroup analyses will be conducted to compare model performance across different scenarios. ML-based prediction models may be superior to logistic or Cox proportional hazards (PH) regression-based models. Previous research studies have compared these approaches, resulting in varying conclusions. Some ML methods have been observed to perform as good as, or may be favourable to, Cox PH or logistic regression for some prediction tasks.^8–12^ Logistic or Cox PH regression methods may perform prediction tasks better or worse than some ML approaches,^11^ but data-driven approaches using ML have been favoured in some studies due to their ability to understand complex relationships in data, which may have an advantageous prediction performance.^12^ It may be more difficult to motivate an ML approach in a resource- or time-limited setting, in particular if data quality or dimensionality is lower and Cox PH or logistic regression methods can complete prediction tasks to a comparable level.

This protocol will use an ensemble method called stacking,^13^ which will combine the predictions of multiple ML models to produce an overall predicted risk score of CRC. Each ML method relies on different statistical assumptions and processes that may reflect different patterns in the data and offer unique insights into the relationships between variables and the outcome.^14^ By leveraging the estimates from each model in the ensemble, the perspectives from diverse model approaches can be integrated to create a more robust and accurate prediction.^15–17^ The performance of the ensemble model approach will be compared with the performance of a Cox PH regression model.

A range of ML methods will be used for the analysis. These algorithms will cluster, classify or identify variables according to their levels of importance in predicting cancer outcomes, aiding in variable selection and prediction model development. Unsupervised ML techniques can explore extensive datasets and examine data without predefined constraints. Supervised ML techniques, however, are still capable of analysing extensive datasets, but in the presence of predefined labels. Using both methods allows for the integration of diverse results from various methodologies, which may strengthen our findings and prediction performance.^16
17^

ML methods and specifically ML prediction modelling have been previously applied to predict certain outcomes for PWH. In clinical care for PWH, ML methods have been applied to predict viral suppression among PWH^18^ and predict who is most at risk of disengaging from ART care.^19^ Similar to the aim of our project, ML methods have been previously applied to develop cancer risk prediction models, but not specifically for PWH.^20
21^ Supervised ML models have been applied to predict the occurrence of cervical precancerous lesions among PWH.^17^ ML methods have also been used to predict comorbidity outcomes as defined by the Charlson Comorbidity Index, which includes cancer, but not as an isolated outcome.^22^ These methods have not yet been applied, to our knowledge, specifically to predict the risk of CRC occurrence among PWH.

In summary, there is a need for updated recommendations and an opportunity to personalise CRC screening recommendations for PWH using robust methods of analysis. This study will aim to develop high-quality risk prediction models by applying various robust ML methods in an ensemble model and comparing it to a baseline Cox PH model. The findings will support model development and provide high-performing tools to help personalise CRC screening recommendations.

### Study aims

The aim of this study is to apply a range of ML methods to analyse comprehensive datasets collected from nationwide demographic and health registers in Sweden to develop CRC risk prediction models for PWH, additionally using data from PWoH and compare the performance to a Cox PH regression model prediction baseline. Additionally, the aim is to evaluate the importance of variables to the prediction models.

## Methods and analysis

### Data sources

Data from the Swedish National HIV Register (InfCareHIV),^7^ the National Cancer Register,^23^ Longitudinal Integration Database for Health Insurance and Labour Market Studies (LISA),^24^ the Total Population Register,^25^ National Cause of Death Register,^26^ National Patient Register^27^ and the National Prescribed Drug Register^28^ will be used in this study.

The Swedish National demographic and health registers, similar to those in other Nordic countries, stand out from the majority of the world through their use and collection of highly detailed nationwide data on an individual level.^29^ A personal identification number is used to identify individuals and record their data in each individual register.^29^ This number can be used to link the registers for research purposes. The linking of the registers is usually performed by Statistics Sweden and the National Board of Health and Welfare. The data delivered usually includes a pseudonymised personal identification number, with the Board keeping the key for identification. Swedish Quality registers are created with the purpose of ensuring equal care development in a specific area of healthcare.^30^ This allows for the collection of highly detailed data relating to specific diseases, conditions, exposures or outcomes of interest. These types of registers are used to monitor rates and diseases, and provide highly detailed data relating to a specified outcome for research.

#### Swedish National HIV Register (InfCareHIV)

The InfCareHIV Register includes data on more than 99% of those diagnosed with HIV in Sweden.^7^ When people are diagnosed or when they immigrate to Sweden with an HIV diagnosis, they are informed that their data will be included in the register but that they may opt-out, and that they may opt-out at any time in the future if they are included. InfCareHIV has collected data from all HIV clinics across Sweden since 2003, and earlier data has been retrospectively added.^7^ The register includes demographic variables, such as legal sex and country of birth, as well as variables relating to HIV acquisition such as date of first positive HIV test and the most likely mode of HIV acquisition. At every follow-up visit, routine measures, such as HIV-RNA levels, CD4(+) T cell counts and current ART, are included in the register.

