#### National Cancer Register

The National Cancer Register, managed by the National Board of Health and Welfare, includes all cancer diagnoses in Sweden. Reporting to the register is mandatory by law, and the register includes data on the tumour diagnosis, morphological diagnosis, tumour extent at time of diagnosis, time and place where it was reported, and personal demographic information such as date of birth and place of residence.^23^ The quality of the register is high, with around 99% of the tumours morphologically verified.^31^ The purpose of the register is to follow cancer outcome trends in the population, between subpopulations, as well as contribute to research.

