#### National Prescribed Drug Register

The National Prescribed Drug Register, managed by the National Board of Health and Welfare, includes all prescribed drugs distributed in pharmacies in Sweden.^28^ It contains patient, product, prescription, cost and prescriber information.^28^ It includes information on any prescribed drugs dispensed through a pharmacy or on medical devices/consumables.^28^ Trends in prescribed drugs are monitored, and these can additionally be linked to other registers to monitor outcomes.

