#### National Patient Register

The National Patient Register, managed by the National Board of Health and Welfare, provides information relating to diseases and specialist care in Sweden.^27^ It includes information on all inpatient stays, outpatient specialised care, compulsory psychiatric admissions and waiting times in emergency departments in Sweden.^27^ Health trends across the country, quality of care and prevention efforts can be monitored with the register.

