### Study population

The study population will include all resident PWH and PWoH, 18 years or older, born between 1940 and 2008, who resided in Sweden at any time point between 1983 and 2024. The study period will span from 1 January 1983 to 31 December 2024. The inclusion date will be the day the person turns 18, the start date of residency in Sweden, or the study start date, whichever occurs last. Follow-up will continue until emigration, death, end of study time or until 6 months before the first incident of CRC. The outcome of interest is CRC. See figure 1 for an illustration of the inclusion criteria and how inclusion and the follow-up period were defined.

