#### Data preparation

For this study, we will use complete cases only since missing data are minimal. Variables missing more than 10% of the data will be omitted, and after that, any observations with missing data will be dropped.^32^ For the ML analyses, the data will be split 80% into training and 20% into test sets based on follow-up time. The variables in each set will be further prepared to optimise their analysis. Categorical variables will be transformed using one-hot encoding. Normalisation and standardisation of variables will be applied where necessary.

The participants will be matched 1:10 using the entire HIV-negative population in Sweden that fit the criteria. They will be matched on age, legal sex, region of birth and comorbidities including hypertension, chronic obstructive pulmonary disease, diabetes and previous cancer diagnosis.^33
34^ The standardised mean difference of the cohorts will be compared from before and after matching to confirm consistency. Power was calculated using the full anticipated study population consisting of just over 13 000 PWH matched 1:10 to approximately 130 000 PWoH. Median follow-up time is estimated to be at least 10 years in both groups. The expected incidence rate of CRC used for the calculation was the Swedish age-standardised incidence rate reported by the European Commission (129.1 per 100 000 population).^35^ Based on these assumptions and using a two-sided alpha of 0.05, the study is estimated to have 80% power to detect an HR of approximately 1.20 or greater.

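### Adults who immigrate enter the cohort with no Swedish register history, so disease before arrival is under-ascertained, and the matching ignores length of residence

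*Protocol article*

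**What the plan says.** **Entry.** Under Study population, the protocol article admits anyone aged 18 or over "who resided in Sweden at any time point between 1983 and 2024". The inclusion date is the latest of the 18th birthday, "the start date of residency in Sweden, or the study start date, whichever occurs last". No minimum prior residence is stated. The section on the Swedish National HIV Register confirms that some PWH arrive with known infection: "when they immigrate to Sweden with an HIV diagnosis, they are informed that their data will be included in the register".

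**Sources.** The Cancer Register "includes all cancer diagnoses in Sweden", the Patient Register "provides information relating to diseases and specialist care in Sweden", and the Prescribed Drug Register "includes all prescribed drugs distributed in pharmacies in Sweden".

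**Matching.** Data preparation lists the variables: "They will be matched on age, legal sex, region of birth and comorbidities including hypertension, chronic obstructive pulmonary disease, diabetes and previous cancer diagnosis". Immigration date and length of residence are not among them. The same section limits the analysis to complete cases because little is expected to be missing.

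**Outcome.** Follow-up runs at most "until 6 months before the first incident of CRC".

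**The concern.** Each rule is reasonable alone. Together they mean that a person who first arrives as an adult after 1 January 1983 starts follow-up on a day with no earlier Swedish health record. Diabetes, hypertension, COPD, cancer or drug treatment before that day cannot be seen. Register-based diagnoses are normally built from the presence or absence of a record, so unseen history is likely to be coded *no*.

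A recorded *no* would then mean free of disease in a settled resident and unknown in a new arrival. The model could not separate sick from healthy arrivals, and region of birth or migrant status could absorb part of a recording artefact. Both matter here, because the stated aims are risk prediction for PWH and assessment of variable importance, and the intended use is individual decisions in HIV clinics. The planned standardised-mean-difference check compares recorded values, so it could look balanced whatever the true status.

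**Working it through.** The plan gives no figure on this point, so there is none to reproduce. The mechanism can be checked from the text. Any size is illustrative.

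**1. Does the gap follow from the rules?**
- Entry for a first-time adult immigrant after the study start is the first day of residency (Study population).
- The cancer, specialist-care and drug sources are described as covering Sweden (Data sources).
- Swedish records before entry are therefore absent. A look-back window defined in the supplement could not restore them.

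**2. Would the safeguards catch it?** The 10% omission rule, the complete-case rule and the incomplete-data sensitivity analysis all act on values coded as missing. An absent record is normally coded as zero, so none of them would respond.

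**3. How far could recording fall?** Assume a share *s* enters by immigration with no recorded history, and that true prevalence *p* is the same in immigrants and others. Then:
- sensitivity of the flag = 1 − s
- recorded prevalence = p(1 − s)
- share of recorded negatives who have the condition = ps / (1 − p(1 − s))

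With p = 5% (assumed):

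| s (assumed) | Sensitivity | Recorded prevalence | True cases among recorded negatives |
|---|---|---|---|
| 0.2 | 0.8 | 4% | 0.01/0.96 = 1.0% |
| 0.4 | 0.6 | 3% | 0.02/0.97 = 2.1% |
| 0.6 | 0.4 | 2% | 0.03/0.98 = 3.1% |

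**4. What could this do to an individual prediction?** Suppose the model is right for immigrants on average but cannot see the condition. Everyone in the group then receives relative risk 1 + p(HR − 1). All inputs are assumed.
- p = 0.15, HR = 1.5: 1.075. Those with the condition get 1.075/1.5 = 0.717 of their true risk (28% too low). Those without it get 7.5% too much.
- p = 0.10, HR = 1.3: 1.03, and 1.03/1.3 = 0.792 (21% too low, 3% too high).
- p = 0.25, HR = 2.0: 1.25, and 1.25/2.0 = 0.625 (37.5% too low, 25% too high).

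This is lost discrimination within the group, not miscalibration of the group as a whole.

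**5. What about a first colorectal cancer?** An error needs a cancer diagnosed abroad that is later registered in Sweden as new. Because follow-up stops six months before the diagnosis, one registered within six months of arrival would end follow-up before it began and so drops out. Only later registrations remain.

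**6. What would a residence requirement cost?** Lost PWH person-time = m × d / 10, where *m* is the share entering as adult immigrants (assumed 0.3-0.7), *d* is the delay in years (1-2), and 10 is the protocol's minimum expected median follow-up in years, used here as if it were each person's follow-up. The range is 0.3 × 1/10 = 3% to 0.7 × 2/10 = 14%.

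**The case against.** **The measurement date is not stated.** The text fixes when follow-up starts, not when comorbidities are measured for matching or prediction. Variable detail is deferred to a supplement, and the inclusion diagram is not available. Measurement at entry is not obvious either: many residents enter at 18, when COPD or previous cancer would be rare, and LISA data begin only in 1990. If status is updated later, chronic disease in immigrants will be picked up through ordinary care. This stands in part. Later updating would shrink the gap but leave the period after arrival affected, and the text does not promise it.

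**Not everyone is misclassified.** A reader might infer that the predictors, the matching and the outcome are wrong for all immigrants. The documents do not support that. Arrivals without earlier disease are coded correctly, and returning residents may have older Swedish records. Under-ascertained is the accurate word.

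**Much of the error is shared by PWH and people without HIV.** Matching on region of birth makes many controls immigrants with the same gap, and migrant status is in the linked data. This largely stands, although length of residence can still differ within a region of birth.

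**An inflated HIV hazard ratio.** A reader might also infer that the HIV effect is biased upwards. If only PWH lacked history, the factor would be 1 + m·p·(HR − 1), from 1 + 0.3 × 0.10 × 0.3 = 1.009 to 1 + 0.7 × 0.25 × 1.0 = 1.175. That requires an index date such as HIV diagnosis or entry to HIV care, which the protocol does not state, and controls without the same gap. The main aim is also prediction, not estimation of that ratio.

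**Conclusion.** The point holds as under-ascertainment. Under the stated entry rule, comorbidity, previous cancer and drug use before arrival are unseen at inclusion for adults who first immigrate during the study period. The gap is likely to read as *no*, and the matching does not account for length of residence. That coding is an inference, because neither the coding nor the measurement date is given.

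The overall size cannot be computed from the document. The ranges shown rest wholly on assumed immigrant shares, prevalences and hazard ratios, and on no later updating of covariates. The effect on first colorectal cancer is probably small. The text does not support a claim that the HIV hazard ratio is biased by a given amount. The point still merits a change, because it bears on prediction and variable importance and the remedy needs no new data source.

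**What to change.** Amend Study population and Data preparation as follows:

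- State the date at which comorbidities, previous cancer and drug use are measured. Add time since immigration on that date, taken from the Total Population Register, to the matching variables and the predictor set. If that date is the inclusion date, the variable is zero for every adult immigrant and only marks entry by immigration, so the date matters.
- Refit the models with entry delayed until a minimum prior residence has passed (for example 1-2 years), excluding anyone with a colorectal cancer record before that point.
- Keep all available earlier history for long-term residents. One short look-back imposed on everyone would discard valid older diagnoses.
- Report discrimination and calibration separately for short and long residence.

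**Cost.** Protocol wording and analysis code, somewhat harder matching, extra analyses, and in the refit the loss of the first 1-2 years after immigration: about 3-14% of PWH person-time under the assumptions above. Disease treated abroad and not recorded in Sweden during the delay would stay invisible, so the refit reduces the problem but does not remove it.
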